## Abstract

Segmental mandibular resection may be indicated as a treatment in, for example, advanced stages of oral squamous cell carcinoma (OSCC). Osseous reconstruction of these defects is a fundamental part of static and dynamic masticatory rehabilitation, particularly when dental implants are required. The Segmental Mandibular Defect Reconstruction (SMDR) Registry aims to generate real-world evidence on SMDR through an international, prospective, multicentre case series designed as a registry. While OSCC is a common indication for segmental mandibular resection, the SMDR Registry also aims to capture outcomes for rarer mandibular conditions and the increasing number of collateral damage cases resulting from systemic medication therapies (antiresorptive drugs, immunotherapeutics) or irradiation, which may likewise lead to medication-related osteonecrosis of the mandible (MRONJ) or osteo(radio)necrosis with tumour-like segmental resection of the mandible, highlighting the value of an international database for these less frequent pathologies. Primary objectives are to describe the patient population and current treatment modalities, describe the outcomes and adverse events (AEs) for different treatment modalities, and identify potential predictors for successful autologous reconstruction of SMDs. Approximately 300 patients with a mandibular lesion resulting from bisphosphonate- and immunomodulatory drug-induced osteonecrosis of the mandible, ameloblastoma or osteosarcoma of the mandible, oral metastases related mandibular lesions indicated for segmental resection, or OSCC undergoing SMDR or intending to undergo one- or two-stage reconstruction will be prospectively recruited over a 36-month period. Baseline information, treatment details, and outcome measures will be documented. All treatments will be per the usual practice at participating sites. Outcome measures include clinical, patient-reported, and radiological outcomes; AEs related to the condition and/or treatment with a possible influence on the outcome will be recorded.

## 1. Introduction

Mandibular defects requiring reconstruction are common and occur after treatment of primary diseases, such as resection of benign or malignant lesions, inflammation, osteo(radio)necrosis, or as a result of trauma [1,2,3]. Management and reconstruction of segmental mandibular defects is challenging, as these defects can lead to severe dysfunction, facial disfigurement, and reduced quality of life, among others [4]. Segmental mandibular defect reconstruction (SMDR) is required to reconstruct the defect with the aim to restore function and aesthetics [5,6]. Manifold options exist for SMDR, including different graft types, donor sites, types of plates, and materials [7]. For transplanted bone grafts, the position, quality and quantity of transplanted bone into the mandible are crucial for later dental rehabilitation, which is one of the priorities in the restoration of functionality. After SMDR, it is known that the number of dentally rehabilitated patients is quite low (15–20%) [8,9,10,11], which is also reflected in our clinical experience, yet few studies describe the rates of and barriers to implant completion after resection. Pogrel et al. reported that 20% to 24% of patients who had osseous reconstruction of mandibular defects went on to have implants, but the reasons why patients did not have implants were not explored [12].

SMDR is further complicated by the debate around mandibular reconstruction timing, which is divided between proponents of one-stage surgery and two-stage surgery [4]. While immediate reconstruction performed in the same surgery as the tumour excision (one-stage surgery) allows for a shorter recovery period, it is technically demanding; in contrast, delayed reconstruction (two-stage surgery) allows for a period of observation to monitor recurrence and enables maturation of the wound bed before bone grafting [4,7]. However, it remains unclear which algorithm (one-stage or two-stage) has better outcomes in terms of position, quality and quantity of transplanted bone, and the effect of postoperative irradiation on transplanted bone. Continuous improvement in surgical resection and reconstruction techniques [13,14] has led to better patient outcomes. Modern treatment planning for patients undergoing segmental mandibular defect reconstruction after mandibular resection for tumours or medication-related osteonecrosis (MRONJ) integrates computer-aided design (CAD), advanced imaging software, segmentation techniques, customisable implants, and 3D models to enable precise, patient-specific surgical planning and reconstruction. Further, health-related quality of life (QoL) studies have shown significantly improved QoL in patients undergoing one-stage surgery [7]. Nevertheless, morbidity and incomplete rehabilitation still persist [15].

The disease variability and complexity of SMDR treatment options mean the effectiveness of the individual factors cannot be easily assessed. A registry gathering standardised information will provide medical and clinical evidence to assist clinical decision-making.

We have designed an international registry to prospectively collect data on patients undergoing reconstruction following segmental mandibular resection for OSCC, osteosarcoma, ameloblastoma, bisphosphonate- and immunomodulatory drug-induced osteonecrosis, and other metastatic mandibular lesions primary to OSCC. The goals are to describe the patient population, current treatment modalities, and outcomes and adverse events (AEs), as well as identify potential predictors for successful autologous reconstruction of segmental mandibular defects.

This registry aims to generate a database to drive future clinical research, generate focused study hypotheses, and answer unforeseen questions concerning the care and outcomes in this patient population.

## 2. Materials and Methods

### 2.1. Study Design and Setting

This is an observational study designed as an international, prospective, multicentre case series serving the function of a registry on patients undergoing the following segmental mandibular resection for OSCC, osteosarcoma and ameloblastoma, bisphosphonate- and immunomodulatory drug-induced osteonecrosis, and other metastatic mandibular lesions arising from malignancies originating in distant organs such as the lung, breast, kidney, and liver. Table 1 summarises the study sites currently included.

### 2.2. Objectives

Aside from collecting data into a large registry database on patients undergoing reconstruction following segmental mandibular resection for OSCC, osteosarcoma and ameloblastoma, bisphosphonate- and immunomodulatory drug-induced osteonecrosis, and other metastatic mandibular lesions rising from malignancies originating in distant organs such as the lung, breast, kidney, liver and prostate, the specific objectives are to (1) describe the patient population and current treatment modalities, (2) describe the outcomes and AEs for different treatment modalities, and (3) identify potential predictors for successful autologous reconstruction of segmental mandibular defects.

### 2.3. Study Procedures

Baseline information, treatment details, and outcomes will be collected in a customised, searchable database. All treatments will be performed according to the usual practice at participating sites; study-specific treatments, selection of devices or materials, and surgical or imaging techniques are not dictated in the study protocol, except for the prospective collection of a standardised set of data (demographic information including comedication, nicotine use, oral hygiene status, history of bisphosphonate treatment, immunomodulatory drug therapy, bone disease and comorbidities, tumour characteristics, adjuvant treatments, surgical parameters, osseous reconstruction details, additional surgeries, pathological assessment, clinical and patient-reported outcomes, and condition and treatment-related AEs). Post-treatment care and follow-up visits will be conducted according to the standard procedures at participating sites. Table 2 shows the inclusion and exclusion criteria.

### 2.4. Recruitment

A recruitment period of 3 years (36 months) is planned to enrol 300 eligible patients. Patient enrolment will be consecutive and competitive (i.e., with no limit in the number of patients enrolled at each site). Potentially eligible patients will be identified by an investigator and/or adequately trained member of the research team at the sites based on the patients meeting all the inclusion and none of the exclusion criteria, ideally after initial pathological/histologic diagnosis of mandibular involvement by oral tumours (such as OSCC, osteosarcoma, and ameloblastoma), bisphosphonate- or immunomodulatory drug-induced osteonecrosis, and mandibular lesions from metastatic diseases have been confirmed and the patients have been scheduled for surgery.

If a patient wishes to participate, a designated member of the research team will explain the informed consent process, including the purpose of the registry, the procedures, the potential risks and benefits, alternatives to participation, and data protection. Patients will also be informed about the possible future use of their de-identified data collected from the current registry for future research projects. Each patient choosing to participate will then sign and date an informed consent form. Consent will be obtained, where possible, before mandibular resection; if it is not possible (from the patient or the surrogate), the patient may provide consent after treatment up until the first standard-of-care follow-up visit, given the purely observational nature of the registry.

All patients who provided consent will be allocated a unique patient number. Each site will keep an Identification List linking patient numbers with their personal information. This Identification List will always be kept safe and in a locked place. Sites will not be allowed to share the Identification List with any third party except for the sponsor representative, legal authorities, and EC/IRB, who may have access to the Identification List during monitoring or auditing activities performed on-site. Figure 1 shows the planned patient flow.

### 2.5. Data Collection

#### 2.5.1. Baseline Information

Demographic (sex and year of birth) and somatometric data (height and weight) will be recorded. Medical and lifestyle history data to be recorded will include data on OSCC, osteosarcoma of the mandible, ameloblastoma, oral metastases, and bisphosphonate- or immunomodulatory drug-induced osteonecrosis of the mandible. For OSCC, data on nicotine consumption and use of antiresorptive drugs (bisphosphonates or denosumab) will be collected. For osteosarcoma of the mandible, data on the history of genetic disorder, fibrous dysplasia and chronic osteomyelitis will be collected. For ameloblastoma, a history of dentigerous cyst, impacted teeth, injury to the mouth or jaw, pulpitis, or Gorlin–Goltz syndrome will be recorded. For oral metastases, a history of primary cancer in specified anatomic regions such as the lung, breast, kidney, or liver will be recorded. For osteonecrosis of the mandible, presence (yes/no) will be recorded, as well as the history of use of bisphosphonates and/or immunomodulatory drugs.

Comorbidities will be assessed using the Charlson Comorbidity Index [16,17]. Tumour characteristics to be recorded include the date of diagnosis, the tumour location, and the location of oral lesions due to metastases. Cancer staging will be documented according to the TNM system (8th edition [18]), including clinical and pathological staging. For this registry, for clinical staging of the data, the stage and cTNM method of assessment will be documented, and for pathological staging, the date and stage of pTNM will be documented.

For bisphosphonate- and/or immunomodulatory drug-induced mandibular osteonecrosis, the location as well as the staging (at risk or stage 0–3) will be documented, with “at risk” being the lowest category and “Stage 3” being the highest category. The classification based on Morton and Simpson’s theory will be documented as minor, moderate, or major [19].

If a panendoscopy is performed, the data and presence of simultaneous distant and/or local secondary carcinoma will be collected.

#### 2.5.2. Treatment Details

Both adjuvant treatment and surgical parameters will be collected. For adjuvant therapy, the dates (start and end) and types (radiotherapy, chemotherapy or targeted therapy and/or immunotherapy) will be recorded. Surgical parameters will be split into the tumour and segmental mandibular resection, the osseous reconstruction, and any additional surgeries related to mandibular reconstruction or dental implants. For tumour and segmental mandibular resection, the date and duration of surgery (skin-to-skin time in minutes) and length of hospital stay will be recorded. Additionally, for the resection details, the use of virtual surgical planning (VSP) (if used, including the use of 3D-printed biomodels and cutting guides) and the surgical approach will be documented. Further details of the mandibular defect (documented according to Brown’s classification [20]), as well as bone defect length, local soft tissue resection, and neck dissection, will be recorded.

For osseous reconstruction, the date of osseous reconstruction (if different from resection surgery) and reasons if not performed within 18 months after resection, as well as the use of VSP for osseous reconstruction (if used, including 3D-printed biomodels and cutting/drilling guides), will be recorded.

In cases of one-stage osseous reconstruction, the reasons for this choice will be documented, plus details of the bone and soft tissue flaps used, the fixation and osteosynthesis methods (including whether a 3D-printed biomodel from VSP was used), and supplementary bone graft, if applicable. Similarly, in cases of two-stage osseous reconstruction, the reasons for this choice will be documented, plus details of the first stage of mandibular resection and temporary alloplastic bridging with or without a solitary soft tissue flap. This will include details on the use of VSP for temporary alloplastic reconstruction, the use of independent soft tissue flaps, and fixation and osteosynthesis methods. Additionally, for the second stage of osseous reconstruction, the following aspects will be recorded: date and duration of surgery, length of hospital stay, use of VSP for osseous reconstruction, as well as details on use of bone and soft tissue flaps, fixation and osteosynthesis methods, and use of additional supplementary bone graft or collagenous membrane, if applicable.

Data on the additional surgeries related to mandibular reconstruction and dental implants to be recorded include date and duration of surgery, length of hospital stay, and indications for surgery.

### 2.6. Pathological Assessment

The pathological assessment will include staging according to pTNM, resection margins (if performed), histological type and subtype, grading (the poorest differentiation grading within the tumour will be documented), and human papillomavirus status (if tested).

### 2.7. Documented Visits

A summary of data to be collected at each visit is shown in Table 3.

Unscheduled visits may occur at any time due to, for example, a medical emergency; however, these visits will not be recorded in the registry, and information gathered between the scheduled registry visits will be documented at the next regular visit, except for the recording of any treatment-related AEs or if the patient drops out of the registry.

### 2.8. Termination of Participation

Participation in this registry may terminate early for reasons such as withdrawal of informed consent, the patient being found to be ineligible, investigator’s discretion (e.g., patient noncompliance), no osseous reconstruction with autologous bone performed within 18 months from resection, loss to follow-up, death, sponsor’s decision, or other reasons. Early terminations will be recorded in a dropout form, including the circumstances leading to the termination. All patient data collected before termination will be censored as of the day of the official withdrawal. Censored data will be included in the analysis, unless a patient explicitly requested removal of their data.

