### 2.9. Outcome Measures

#### 2.9.1. Clinical Outcomes

Clinical outcomes (Table 2) to be assessed are:Neurological outcomes, including both sensory function in the mandible and the oral cavity, as well as motor function of cranial nerves that include the facial nerve (VII) marginal branch, hypoglossal nerve (XII), and accessory nerve (XI).Dental status, assessed according to the Eichner classification [21,22].Dental rehabilitation, including use, or potential use, of dental implants or equivalent within the reconstructed mandibular segment (date of placement, number and location of implants, type of healing for dental implants, time to function, dental implant status), as well as dentures (prosthodontic use) if the patient is edentulous or partially edentulous.Survival, including both recurrence-free survival (for OSCC, osteosarcoma, ameloblastoma and oral metastases but not for non-tumour conditions such as bisphosphonate- and/or immunomodulatory drug-induced osteonecrosis) and overall survival (applicable for OSCC, osteosarcoma, ameloblastoma, oral metastases, and non-tumour conditions such as bisphosphonate- and/or immunomodulatory drug-induced osteonecrosis).

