**Patient-reported outcomes**										
**OHIP**	X		X	X	X	X	X	X		X
**EQ-5D-5L**	X		X	X	X	X	X	X		X
**Patient satisfaction**					X	X	X	X		X
**Adverse events**		X	X	X	X	X	X	X	X	X
**Radiological assessment ^5^**	X	X	X	X	X	X	X	X	X	X

* Postoperative FU visits with the defined time windows are calculated from the day of mandibular resection (i.e., day 0) and reconstruction (if the patient undergoes primary reconstruction).^1^ Post-second-stage reconstruction visits will be calculated from the day of secondary reconstruction (day 0). Patients will be followed up for a maximum of 2 years from the time of mandibular resection. ^2^ Information on adjuvant treatment for the malignant conditions may be available at a different timepoint and will be documented whenever it becomes available. ^3^ Osseous reconstruction can occur on the day of resection (one-stage reconstruction) or on a different day (two-stage reconstruction). ^4^ Additional surgeries may occur at any time after mandibular resection. ^5^ All images will be taken according to the local standard of care and will be collected. Assessments will be performed on available images.

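### The single censoring rule in section 2.8 also covers deaths and leaves the censoring date undefined for lost patients, which conflicts with the survival outcomes in section 2.9.1

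*Protocol article*

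**What the plan says.** Section 2.8 (Termination of Participation) gives the reasons for which participation may end early. They include "no osseous reconstruction with autologous bone performed within 18 months from resection, loss to follow-up, death". Three statements on handling follow:

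- On documentation: "Early terminations will be recorded in a dropout form, including the circumstances leading to the termination".
- On dating: "All patient data collected before termination will be censored as of the day of the official withdrawal".
- On use: "Censored data will be included in the analysis, unless a patient explicitly requested removal of their data".

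No reason is exempted from the dating rule, and the day of official withdrawal is not defined for someone who has died or disappeared.

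Section 2.9.1 (Clinical Outcomes) lists "Survival, including both recurrence-free survival" for the tumour conditions and "overall survival (applicable for OSCC, osteosarcoma, ameloblastoma, oral metastases, and non-tumour conditions" as well. Table 3 collects survival at every visit from surgery onward, and its first footnote sets the horizon: "Patients will be followed up for a maximum of 2 years from the time of mandibular resection".

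Section 2.11 calls the registry exploratory, with no primary or secondary outcomes. It says that data up to dropout will be analysed, and it leaves analysis populations, missing data and protocol violations to an SAP that is not shown. It does not leave the censoring rule to the SAP; section 2.8 fixes that rule.

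**The concern.** Censoring means that follow-up stopped before the event was seen. In overall survival, death is the event. A rule that treats death as a termination, and every termination as censored, removes the events that the outcome counts. For recurrence-free survival, if death is part of the definition (the article does not say), deaths without recurrence disappear in the same way and the outcome becomes freedom from recurrence alone.

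The second difficulty concerns patients who are lost. Nobody lost to follow-up officially withdraws, so the date must be assigned by someone at the site. If it is the day the form is completed, and not the day of last contact, the patient stays in the risk set for a period in which a death could not have been recorded. The estimate then drifts upward.

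At stake is whether the survival figures in the final registry report can be read, and whether an SAP author has to contradict the protocol to produce valid ones.

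**Working it through.** The article states no mortality, loss rate or survival figure, so there is nothing of its own to reproduce. The 300 patients are a feasibility number.

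**1. Deaths: the text read in sequence.** Death is a reason for early termination (2.8). Data of terminated patients are censored as of the official withdrawal, without exception (2.8). Overall survival is an outcome for every condition (2.9.1). Taken together, each death is a censored record.

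The Kaplan–Meier estimate is S(t) = ∏(1 − dᵢ/nᵢ), where dᵢ is the number of deaths and nᵢ the number at risk at each event time. If every dᵢ is 0, every factor is 1 and S(24 months) = 1.00, whatever the true mortality.

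Number of events affected, per 300 patients (assumptions: constant hazards, two-year mortality 10–40%, independent two-year loss 5–20%). With λ = −ln(1 − mortality)/24, μ = −ln(1 − loss)/24 and k = λ + μ, the deaths seen before loss are 300 × (λ/k) × (1 − e^(−24k)):

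- 10% mortality, 20% loss: about 27
- 40% mortality, 5% loss: about 117

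**2. Lost patients: effect of a gap.** Suppose deaths are counted correctly, but lost patients are censored g months after last contact. The gap is an assumption: 3, 6 or 12 months. For scale, the last three scheduled visits in Table 3 are six months apart, with windows of ±2 to ±3 months.

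From month g onward the risk set is inflated by the factor F = 1 + (μ/k)(e^(kg) − 1). Integrating the resulting hazard to 24 months gives

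H = kg − ln F + λ(24 − g)/F, and estimated survival = e^(−H).

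Worked example (40% mortality, 20% loss, g = 12):

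- λ = 0.5108/24 = 0.02128; μ = 0.2231/24 = 0.00930; k = 0.03058
- kg = 0.3670; F = 1 + 0.3040 × 0.4434 = 1.1348
- H = 0.3670 − 0.1265 + 0.2554/1.1348 = 0.4656
- e^(−0.4656) = 0.628 against a true 0.600, an overstatement of 2.8 points

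Overstatement of 24-month survival, in percentage points:

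| Mortality / loss | 3-month gap | 6-month gap | 12-month gap |
|---|---|---|---|
| 10% / 5% | 0.06 | 0.11 | 0.18 |
| 20% / 10% | 0.22 | 0.42 | 0.73 |
| 40% / 20% | 0.82 | 1.57 | 2.78 |

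A simulation with 300,000 patients per scenario agrees with these nine values to within 0.02 points when compared with the correctly censored estimate from the same simulated data. With g = 0 the bias is zero.

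**3. After correction.** With death as the event and lost patients censored at last contact, the same simulation returns the true survival to within about 0.2 points in every scenario (for example 0.7998 against 0.80, and 0.5995 against 0.60).

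**The case against.** The best defence is that the word censored is used loosely here. The sentence speaks of collected data, the next one keeps those data in the analysis, and section 2.11 repeats that data up to dropout are used. That reads like a data cut-off. The dropout form records why participation ended and Table 3 collects survival at each visit, so the deaths stay identifiable. No survival estimator is named, and event definitions are normal SAP content.

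Much of this stands. A reader might infer that deaths will be lost from the database or that the analysts will report 100% survival. The documents do not support that: they show a rule that would have this effect if followed, not an analysis that has followed it. What does not stand is that the cut-off reading settles the matter. It does not say that death counts as an event, and it gives no usable date for a lost patient. Nor is this an omission left to the SAP, since section 2.8 states the rule itself.

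Three further inferences are tempting and should not be drawn:

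- **Adverse event rates are biased downward.** Section 2.11 divides by the total population regardless of dropout. No person-time enters, so the withdrawal date cannot move these rates, and counting surplus person-months says nothing about them.
- **The dental rehabilitation rate is overstated.** That needs a time-to-implant analysis with deaths censored. The article records dates and time to function, but section 2.11 plans only frequencies and summary statistics.
- **The withdrawal date is known to be later than last contact.** The article leaves it undefined. A gap is plausible, but it is an assumption.

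**Conclusion.** The point holds as a contradiction in the wording between sections 2.8 and 2.9.1. For deaths the literal consequence is total: estimated overall survival of 1.00, with roughly 27 to 117 events per 300 patients treated as censored under the assumed mortality and loss. That size depends on the rule being applied as written.

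For lost patients the effect is small to modest and conditional on a gap between last contact and the recorded withdrawal: about 0.1 to 0.7 points at 5–10% loss and 10–20% mortality, and 0.8, 1.6 and 2.8 points for gaps of 3, 6 and 12 months at 20% loss and 40% mortality. All these rates and gaps are assumptions, as are constant hazards and independent loss.

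This should be corrected but does not threaten the registry. It is exploratory, survival is one of several described outcomes, and the fact of death is kept. The planned 300 patients are unaffected.

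**What to change.** Replace the single rule in section 2.8 with one by endpoint, and carry it into the SAP:

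- **Overall survival:** death from any cause is an event on the date of death. All others are censored at the last date known alive.
- **Recurrence-free survival:** state whether death is an event together with recurrence; if so, it counts on its date. Patients without the event are censored at the last disease assessment.
- **Withdrawal date:** use it for censoring only when it is itself the last contact.
- **Dental or graft outcomes:** if any is analysed as time-to-event, treat death as a competing event.

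The cost is one paragraph of wording. The date of death and the date of last contact must be available; if the dropout form does not already hold them, they can be added or taken from visit records. Section 2.13 plans the analysis for May–September 2026, so the wording should be settled before then.
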